## Abstract

**Background:**

Patients with moderate and severe persistent allergic rhinitis (AR) have long-term physical and mental stress, leading to dysfunction of the hypothalamus-pituitary-adrenal (HPA) axis, which results in recurrence of AR. Previous research has proved acupuncture can regulate the function of the neuron-endocrine-immune system and contribute to improving the quality of life of patients with AR. This research aims to investigate the mechanism of acupuncture on the HPA axis in patients with moderate or severe persistent AR.

**Methods/design:**

This randomized controlled trial aims to study the impact of acupuncture on the HPA axis of patients with moderate and severe AR. This research also aims to compare the curative effects of different treatments in three groups of patients: those receiving western medicine, western medicine and conventional acupuncture, or western medicine and mind-regulating acupuncture. We will study the therapeutic effect of acupuncture and the correlation between the changes of therapeutic indexes and experimental indexes after the treatments. Therapeutic indexes include the Visual Analog Scale (VAS) of nasal symptoms and the Rhinoconjunctivitis Quality of Life Questionnaire (RQLQ) for AR patients; experimental indexes include corticotropin releasing hormone (CRH), adreno-corticotropic hormone (ACTH), cortisol (CORT), interleukin 4 (IL-4), and interferon-γ (IFN-γ).

**Discussion:**

The results of this trial will provide evidence for the influence of chronic, long-term, repeated stimulation in patients with moderate and severe persistent AR and the impact of acupuncture on the HPA axis of these patients.

**Trial registration:**

Acupuncture-Moxibustion Clinical Trial Registry, AMCTR-IOR-16000009. Registered on 22 August 2016.

## Background

The impact of allergic rhinitis (AR) is not limited to nasal symptoms. Based on previous studies, AR results in severe dyssomnia which causes a lack of energy during the day. This seriously affects the quality of life and work efficiency of AR patients. In adition, AR has negative impacts on the learning capability, attention, and behavior of children [1]. AR patients experience various unpleasant emotions and conditions, for example, fatigue, anxiety, tension, depression, and low sensibility [2]. A recent study about patients with persistent AR reported that 74% of 166 patients experienced psychological stress. Another study [3] found that the synthesis and secretion of cytokines such as interleukin (IL)-2, IL-6 and interferon (IFN)-γ are induced by psychological stress [4]. Psychological stress leads to imbalance of two groups of T helper cells, Th1 and Th2. The increase in Th2 causes the body to be more susceptible to allergens. Therefore, the initiation of AR includes both biological (allergen) and mental (stress, anxiety, and depression) factors.

At present, conventional medicine treatments can relieve the nasal symptoms of AR effectively. However, the psychology of AR patients is not being addressed by physicians. Attention to the psychological state of AR patients is insufficient and treatment regarding patients’ psychological states is not considered during regular treatment by most ear-nose-throat doctors. This limits the therapeutic effects of the treatments [5]. Clinical research found that the negative emotions of AR patients could be relieved if the acupoints responsible for the depression are relieved and tranquilization is used at the base of regular acupoints. As well as effective relief of the clinical symptoms, quality of life was clearly improved [6]. At the same time, due to the low toxicity and side effects, compliance with treatments increases. However, current research regarding the mechanism by which acupuncture regulates AR is limited. Besides, the index used in most research is mostly restricted to the inflammatory cells and cytokines. This results in a lack of a systemic and integral research approach.

In recent years, much research has proved that acupuncture can regulate the function of the neuroendocrine-immune (NEI) system [7, 8]. By stimulating the body’s “self-regulation system”, acupuncture enables the body to reach a dynamic balance and integration. Current research proves that the NEI system plays an important role in the pathological mechanisms of allergic diseases [9]. The NEI system of patients undergoes significant change under stress conditions. The main component of the NEI system is the hypothalamic-pituitary-adrenal (HPA) axis [10]. Under stress conditions, the body is affected by both physiological and mental factors. These changes can be long-term and excessive, leading to a series of physiological changes by interfering with the function of the neuroendocrine and immune systems. As a result, the Th1/Th2 balance is broken and the increase in Th2 induces a series of allergic diseases such as AR and asthma. This research aims to investigate the mechanism of action of acupuncture on the HPA axis in patients with moderate and severe persistent AR, and to explore the effect of acupuncture on the integral regulation of the immune system from different perspectives and multitargets. This will help to build a theoretical foundation for the therapeutic effect of acupuncture in various diseases.

## Methods

### Ethics and dissemination

Ethical approval for this trial has been granted by the Institutional Review Boards of Beijing University of Chinese Medicine (approval number BZYYYDX-LL-20150208), which is a central ethics committee providing approval for our two centers. Any adjustments to the scheme can only be carried out if the Ethics Committee and the volunteers give approvel after thorough communication. Written informed consent is required for all participants. The findings of the trial will be published in open access peer-reviewed journals.

### Trial design

This is a double-center, randomized controlled clinical trial of moderate and severe persistent AR. It has been registered in the Acupuncture-Moxibustion Clinical Trial Registry (AMCTR-IOR-16000009). This study will be carried out in Dongzhimen Hospital Affiliated to Beijing University of Chinese Medicine and Beijing Chao-Yang Hospital. The whole process will last for 13 weeks. After one week of assessment, participants will be randomly distributed into three groups to receive different treatments for 8 weeks, followed by a 4-week follow-up period. The three types of treatments are conventional acupuncture with western medicine treatment, mind-regulating acupuncture with western medicine treatment, and western medicine treatment (Fig. 1, 2).

**Fig. 1 Fig1:**
[figure not shown]
Study flow diagram. *AR* allergic rhinitis

**Fig. 2 Fig2:**
[figure not shown]
The schedule of enrolment, interventions, and assessments

### Participants

#### Inclusion criteria

Eligible participants should be diagnosed with moderate or severe persistent AR according to the criteria of Allergic Rhinitis and Its Impact on Asthma (ARIA) [11] and should reach the following requirements:Persistent symptoms (> 4 days/week and > 4 weeks/year)Aged 18–60 yearsMean Visual Analogue Scale (VAS) score for nasal symptoms ≥ 4 for 7 days during the screening periodProvide written, informed consent

#### Exclusion criteria

Individuals will be excluded from the study if they have one of the following criteria:Individuals with acute respiratory infection, acute paranasal sinusitis, chronic paranasal sinusitis, organic lesions of the nasal cavity, or history of nasal surgeryIndividuals with paroxysmal respiratory diseases such as asthmaConsumption of H1-antihistamines, steroids, antihistamine formulation, decongestant (applied to nasal cavity, oral cavity, or eyes), corticosteroids, antibiotics, and other medicines within 14 days; specific immunotherapy or systemic steroid treatment within 1 yearTCM physiotherapy or other traditional medicine such as acupuncture, moxibustion, cupping, and nasal inhalation within 14 days; consumption of Chinese medicine for AR within 14 daysWomen who are pregnant, lactating, or undergoing preparation for pregnancyIndividuals with infectious diseases such as tuberculosis or hepatitisIndividuals who have smoked 10 cigarettes or more per day for 10 years or moreIndividuals with scars at most selected acupoints or individuals who are uncooperative during the treatments

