### Recruitment

Volunteers come through public notices and are AR patients of Dongzhimen Hospital Affiliated to Beijing University of Chinese Medicine, Beijing Chaoyang Hospital and community hospitals. After selections, volunteers who satisfy all requirements are required to sign the informed consent. These volunteers will undergo one week of assessment and they are required to fill in the VAS forms on nasal symptoms. After one week, volunteers with a mean Visual Analogue Scale (VAS) of nasal symptoms score of 4 or above for 7 days are selected for this clinical trial. They are required to examine the level of corticotropin releasing hormone (CRH), adreno-corticotropic hormone (ACTH), cortisol (CORT), IL-4, and IFN-γ in the blood. Volunteers who are not eligible are provided regular treatments for 4 weeks.

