### Randomization and blinding

Using SAS 9.3.1 software (SAS Institute Inc., Cary, NC, USA), selected cases will be distributed in a 1:1:1 ratio to generate a randomized grouping table. Envelopes for the randomized grouping table will be prepared; the envelopes used are opaque, numbered in order, and contain the randomized serial numbers for grouping. According to the randomized serial numbers, individuals will be distributed to the observation groups and control group.

Researchers in charge of data collection, data statistics, and data evaluation will be blinded from the group allocation. However, individuals being treated and the physicians will not be blinded from the group allocation due to the different interventions in this trial.

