### Planned interventions

#### Acupuncture treatment

Individuals from the observation groups will undergo either the acupuncture therapy or acupuncture with conventional treatment.Acupoints: Bai Hui (DU20), Yin Tang (EX-HN3), Ying Xiang (LI20), Tai Chong (LR3), He Gu (LI4), Zu San Li (ST36); Da Zhui (DU14), Fei Shu (BL13), Pi Shu (BL20), Gan Shu (BL18), Shen Shu (BL23).Needles: “Andy” disposable sterile stainless needles, size of 0.25 × 40 mmAcupuncture methods: All acupoints are positioned according to the People’s Republic of China, State Standard Name and Location of Acupoints (GB 12346–2006) [12]. In the prone position, Da Zhui (DU14), Fei Shu (BL13), Pi Shu (BL20), Gan Shu (BL18), Shen Shu (BL23) are punctured. Once all acupoints achieve “deqi” (an irradiation feeling deemed to indicate effective needling), stimulation of the needles is manipulated in balancing moves (reinforcing-reducing method) for 30 s. Acupuncture treatments last for 20 min. In the supine position, Bai Hui (DU20), Yin Tang (EX-HN3), Ying Xiang (LI20), Tai Chong (LR3), He Gu (LI4), Zu San Li (ST36) are punctured. Once all acupoints achieve “deqi”, stimulation of the needles is manipulated in balancing moves (reinforcing-reducing method) for 30 s. Acupuncture treatments last for 20 min.

Mind-regulating acupuncture treatment is done with patients in both the prone and supine positions, whereas conventional acupuncture is done only in the supine position.

Acupuncture is carried out thrice a week and lasts for 8 weeks, for a total of 24 treatments in each group.

The western medicine treatment in the two acupuncture groups is the same as that in the western medicine group.

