#### Western medicine treatment

Individuals in the control group will receive western medicine treatment.

According to the guidelines for the treatment of AR recommended by ARIA in 2008 [13], individuals in the control group will receive 2–4 weeks of intranasal corticosteroids, H1-antihistamines, or leukotriene receptor antagonists; after this, a specialized ENT examination will be repeated. An otolaryngologist will adjust the dosage or drug schedule according to the ENT findings, and treatments will be continued. One treatment course will last for 8 weeks.

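### One exclusion criterion rests on conduct during treatment, which starts only after randomisation, so as worded only randomised patients can meet it

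*Protocol article*

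**What the plan says.** In the protocol article, Exclusion criteria opens with "Individuals will be excluded from the study if they have one of the following criteria". The last item of the list pairs scars at the acupoints with "individuals who are uncooperative during the treatments".

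Trial design gives the order of events: "After one week of assessment, participants will be randomly distributed into three groups to receive different treatments for 8 weeks". A four-week follow-up comes after that. Recruitment places selection earlier still: "After selections, volunteers who satisfy all requirements are required to sign the informed consent", with the assessment week to follow.

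The arms differ in what they ask of patients. For the acupuncture arms, "Acupuncture is carried out thrice a week and lasts for 8 weeks, for a total of 24 treatments in each group". Between those two arms, "Mind-regulating acupuncture treatment is done with patients in both the prone and supine positions, whereas conventional acupuncture is done only in the supine position". For the third arm, "Individuals in the control group will receive western medicine treatment". Randomization and blinding states that "individuals being treated and the physicians will not be blinded from the group allocation".

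**The concern.** An exclusion criterion should be something that can be settled before allocation. This one refers to behaviour in a period that does not begin until the patient has been randomised. If a site follows it literally, a randomised patient leaves the study because of how he or she behaved under a known treatment.

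The three arms then cease to be the groups that randomisation formed. If the kind or number of patients lost differs between arms, the ANOVA between groups compares selected groups, and a difference can appear or be hidden without any treatment effect. Exclusion from the study, as opposed to stopping treatment, also suggests that VAS, RQLQ and blood samples would no longer be collected. Data never collected cannot be restored by a later choice of analysis set.

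**Working it through.** The point is one of timing, and the plan gives no figure to reproduce. The check has two parts.

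**1. Order of events**

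| Step | Section | Study treatment under way? |
|---|---|---|
| Selection and consent | Recruitment | No |
| One-week assessment, mean VAS of at least 4 | Recruitment; Inclusion criteria | No |
| Randomisation 1:1:1 | Trial design; Randomization and blinding | No |
| 8 weeks of treatment | Trial design | Yes |
| 4 weeks of follow-up | Trial design | Finished |

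There is no run-in on study treatment, and acupuncture in the 14 days before is itself an exclusion. Cooperation during treatment therefore cannot be observed before randomisation. On the literal wording, the set of people who can meet the criterion lies wholly within the randomised patients.

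**2. Size, for illustration only**

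Inputs:
- From the document: 108 patients in a 1:1:1 ratio, so 108/3 = 36 per arm; significance level 0.05.
- Assumed: the test is two-sided (the document does not say); a fraction f of one arm is removed and none of the comparator; those removed differ by d SD on average from those kept; the SD is 1 in both arms. Neither f nor d is in the document. The top value of f, 20%, equals the planned drop-out allowance, but placing all of it in one arm is an assumption.

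Formulas:
- The full-arm mean equals the mean of those kept plus f × d, so the bias is f × d in absolute value.
- Standard error of the difference: SE = √(1/[36(1 − f)] + 1/36).
- Two-sided type I error with no true effect: Φ(bias/SE − 1.96) + Φ(−bias/SE − 1.96).

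Worked case, f = 0.20 and d = 1.0: bias = 0.20 SD; SE = √(1/28.8 + 1/36) = 0.25; bias/SE = 0.80; type I error = Φ(−1.16) + Φ(−2.76) = 0.123 + 0.003 = 12.6%.

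| f | d (SD) | Bias (SD) | Type I error |
|---|---|---|---|
| 5% | 0.5 | 0.025 | 5.1% |
| 5% | 1.0 | 0.05 | 5.5% |
| 10% | 0.5 | 0.05 | 5.5% |
| 10% | 1.0 | 0.10 | 7.0% |
| 20% | 0.5 | 0.10 | 6.9% |
| 20% | 1.0 | 0.20 | 12.6% |

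With few removals the effect is negligible. It becomes material only if removals in one arm approach the planned drop-out rate and those removed differ clearly from the rest. Similar removals in the comparator arm would offset it in part or in full.

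**The case against.** The best defence is that the phrase is a clumsy screening criterion. It stands in an eligibility list, in the same item as acupoint scars, which concerns whether needling is feasible, and Recruitment settles selection before the assessment week. The intended sense may well be patients expected to be uncooperative. That is plausible and it lowers the severity. It does not remove the point, because the text does not say so and two centres have to apply it as it stands.

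A second defence is that analysis sets and the handling of non-adherence are commonly left to the full protocol or analysis plan. That is right, and the absence of such text here is no fault. The fault is in a criterion that the article does state. An analysis set defined elsewhere would not bring back outcomes that were never collected after a patient was excluded.

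A reader might also infer more than the article supports:
- *That unblinded staff remove such patients and discard their data.* No section says who judges cooperation, describes a removal procedure or says that data are dropped. Those who collect, evaluate and analyse data are blinded.
- *That removals fall mainly on the acupuncture arms.* The 24 sessions make this plausible, but every arm has 8 weeks of medication, weekly VAS and RQLQ and three blood collections, and Western medicine treatment also provides for a repeat ENT examination. Cooperation can fail in any arm.
- *That the bias favours acupuncture.* This needs uncooperative patients to have worse outcomes. Patients who stop attending because they feel better would push the other way.

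**Conclusion.** The criterion is wrong as written: by the protocol's own sequence, only randomised patients can meet it. Because the arms demand different cooperation and treatment is open-label, exclusions under it could differ by arm and bias the comparison of each acupuncture arm with western medicine alone. The comparison between the two acupuncture arms is less exposed, since both have the same number of sessions and differ in the positions used.

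Neither direction nor size can be determined from the document. The range of about 0.03–0.20 SD rests entirely on the assumed 5–20% removal from one arm and the assumed 0.5–1.0 SD difference, and should be read as scale and not as an estimate.

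Severity is moderate. The study describes itself as exploratory, and the phrase has a plausible harmless reading. On the other side, the correction is nearly free, and follow-up lost through the literal reading could not be recovered.

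**What to change.** Two sentences.

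1. In Exclusion criteria, replace the phrase with a judgement made before randomisation, for example: *unwilling or unable to attend the planned visits, as judged at the end of the screening week*.
2. State that non-cooperation after randomisation is recorded as non-adherence and is not a ground for exclusion from the study: VAS, RQLQ and blood collection continue where the patient consents, and the patient is analysed in the assigned arm.

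The cost is the two sentences and the effort of following non-adherent patients. The estimated effect may be slightly smaller because those patients are kept. Patients already randomised and excluded under the present wording, if any, should be reported by arm with the reason.

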### Recruitment

Volunteers come through public notices and are AR patients of Dongzhimen Hospital Affiliated to Beijing University of Chinese Medicine, Beijing Chaoyang Hospital and community hospitals. After selections, volunteers who satisfy all requirements are required to sign the informed consent. These volunteers will undergo one week of assessment and they are required to fill in the VAS forms on nasal symptoms. After one week, volunteers with a mean Visual Analogue Scale (VAS) of nasal symptoms score of 4 or above for 7 days are selected for this clinical trial. They are required to examine the level of corticotropin releasing hormone (CRH), adreno-corticotropic hormone (ACTH), cortisol (CORT), IL-4, and IFN-γ in the blood. Volunteers who are not eligible are provided regular treatments for 4 weeks.

### Randomization and blinding

Using SAS 9.3.1 software (SAS Institute Inc., Cary, NC, USA), selected cases will be distributed in a 1:1:1 ratio to generate a randomized grouping table. Envelopes for the randomized grouping table will be prepared; the envelopes used are opaque, numbered in order, and contain the randomized serial numbers for grouping. According to the randomized serial numbers, individuals will be distributed to the observation groups and control group.

Researchers in charge of data collection, data statistics, and data evaluation will be blinded from the group allocation. However, individuals being treated and the physicians will not be blinded from the group allocation due to the different interventions in this trial.

### Planned interventions

#### Acupuncture treatment

Individuals from the observation groups will undergo either the acupuncture therapy or acupuncture with conventional treatment.Acupoints: Bai Hui (DU20), Yin Tang (EX-HN3), Ying Xiang (LI20), Tai Chong (LR3), He Gu (LI4), Zu San Li (ST36); Da Zhui (DU14), Fei Shu (BL13), Pi Shu (BL20), Gan Shu (BL18), Shen Shu (BL23).Needles: “Andy” disposable sterile stainless needles, size of 0.25 × 40 mmAcupuncture methods: All acupoints are positioned according to the People’s Republic of China, State Standard Name and Location of Acupoints (GB 12346–2006) [12]. In the prone position, Da Zhui (DU14), Fei Shu (BL13), Pi Shu (BL20), Gan Shu (BL18), Shen Shu (BL23) are punctured. Once all acupoints achieve “deqi” (an irradiation feeling deemed to indicate effective needling), stimulation of the needles is manipulated in balancing moves (reinforcing-reducing method) for 30 s. Acupuncture treatments last for 20 min. In the supine position, Bai Hui (DU20), Yin Tang (EX-HN3), Ying Xiang (LI20), Tai Chong (LR3), He Gu (LI4), Zu San Li (ST36) are punctured. Once all acupoints achieve “deqi”, stimulation of the needles is manipulated in balancing moves (reinforcing-reducing method) for 30 s. Acupuncture treatments last for 20 min.

Mind-regulating acupuncture treatment is done with patients in both the prone and supine positions, whereas conventional acupuncture is done only in the supine position.

Acupuncture is carried out thrice a week and lasts for 8 weeks, for a total of 24 treatments in each group.

The western medicine treatment in the two acupuncture groups is the same as that in the western medicine group.

#### Western medicine treatment

Individuals in the control group will receive western medicine treatment.

According to the guidelines for the treatment of AR recommended by ARIA in 2008 [13], individuals in the control group will receive 2–4 weeks of intranasal corticosteroids, H1-antihistamines, or leukotriene receptor antagonists; after this, a specialized ENT examination will be repeated. An otolaryngologist will adjust the dosage or drug schedule according to the ENT findings, and treatments will be continued. One treatment course will last for 8 weeks.

